#### Sample size.

Research question 1 will be addressed using regression methods; therefore, a power calculation has been performed using RStudio (version 2024.04.1 + 748, Posit Software) and pwr library (version 1.30) to obtain an *R*_*2*_ value of 0.09, which is roughly equivalent to a medium effect as Cohen’s *d*. A sample of 187 children would permit the explanation of 9% of the variance with 12 predictor variables, 80% power and 5% chance of type 1 error. To account for attrition an additional 10% will be recruited to give a final sample size of 206 children. Up to 50 preschool teachers will be recruited, but fewer teachers may be required if they elect to take part with several children.

Children and teachers will be eligible if they do not have any identified genetic, metabolic, syndromic, or progressive neurological disorder, (e.g., epilepsy, Down or Rett Syndrome, Autism Spectrum Conditions, Attention Deficit Hyperactivity Disorder, Tuberous Sclerosis, Neurofibromatosis, Fragile X Syndrome,).

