### The current investigation

This study will assess the relationship between teacher-child neural synchrony, child development of EFs and school readiness in preschool-age children. Children will be assessed cross-sectionally between the ages of 2 and 7 years. Children will complete EFs, vocabulary and school readiness assessments. Additionally, children and teachers will take part in interactive tasks whilst undergoing dyadic electroencephalography (EEG) and electrocardiogram (ECG) recordings to assess teacher-child interpersonal neural synchrony.

Study objectives and research questions:

Which teacher-child behavioural interaction characteristics are associated with individual differences in preschool children’s executive function and school readiness?Does teacher-child neural synchrony during scaffolded tasks predict learning outcomes, including executive function and school readiness?

Explorative analyses:

Do different forms of teacher scaffolding (e.g., patterns of multimodal ostensive signals or dialogic reading framework) relate differentially to behavioural or neural synchrony?How do teacher individual characteristics (e.g., EF, stress, temperament) moderate the relationship between scaffolding and child outcomes?

The study protocol will be described in eight main sections: study preparation, EFs tasks, school readiness assessment, vocabulary assessment, teacher-child interaction tasks, creative problem solving tasks, neurophysiological measures and questionnaire measures.

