#### Recruitment overview.

Participants will be preschool children aged 2–7 years and previously unacquainted preschool teachers. The selected age range of 2–7 years reflects a critical developmental window during which core executive functions—such as working memory, cognitive flexibility, and inhibition—undergo rapid maturation [18,20]. This range also aligns with the typical age of preschool attendance in Singapore, where children begin preschool as early as age 2 or 3 years and transition to primary school at age 6 or 7 years [45]. Participants will be recruited via collaborations with preschool groups and independent participants. Children and teachers will be invited to the lab for 2 sessions lasting up to 3.5 hours each, ideally less than 2 weeks apart. Teachers will be invited to an additional individual assessment session lasting up to 3 hours. In this session teachers will complete individual EFs and intelligence assessments.

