### Analysis plan

A combination of standard regression and machine learning methods will be used to identify characteristics of teacher-child social interactions that significantly predict EFs and school readiness scores (Research Question 1). Examples of behavioural indices of interaction quality are ostensive signals (gaze, speech, gestures), number of teacher prompts used, difficulty level of teacher prompts, number of prompts responded to by the child and complexity of child response. These behavioural indices of interaction quality along with individual teacher and child characteristics, such as personality or temperament, will be used to as factors to predict child EFs and school readiness. Data reduction methods such as least partial squares or principal components analysis may be used to reduce the dimensionality of data and prevent multicollinearity issues. These reduced factors will be used to predict school readiness and EFs.

To explore which characteristics of teacher-child neural coupling are associated with successful teacher-child interactions (Research Question 2) indices of neural coupling will be calculated from the dyadic EEG data and will be analysed in relation to learning outcomes on scaffolding tasks, as well as the behavioural indices of interaction quality that explain the most variance in EFs and school readiness. Examples of indices of neural coupling are weighted phase lag index (wPLI) or partial directed coherence (PDC). wPLI is a non-directional measure of neural coupling which will describe linear dependencies between the phase neural oscillations between two channels. This may be used to measure connectivity within the teacher or child’s brain, as well as between the teacher and child’s brains. PDC, alternatively, is a directed measure of connectivity and will provide additional information about the directionality of the flow of information. We will also explore the extent to which synchrony in the participants ECG is associated with successful teacher-child interactions.

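### The 187 children are counted as independent although at most 50 teachers serve them, so the stated 80% power and 5% error hold only if the within-teacher correlation is about zero or the predictors vary independently of teacher

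*Protocol article*

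**What the plan says.** The Sample size section bases the target on research question 1 and a regression power calculation: "A sample of 187 children would permit the explanation of 9% of the variance with 12 predictor variables", with "80% power and 5% chance of type 1 error". Ten per cent is added for attrition, giving 206 children to recruit. On teachers it says: "Up to 50 preschool teachers will be recruited, but fewer teachers may be required if they elect to take part with several children". It gives no intraclass correlation, design effect or expected number of children per teacher.

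The Analysis plan section then says: "A combination of standard regression and machine learning methods will be used to identify characteristics of teacher-child social interactions". The predictors listed there are behavioural indices of the interaction together with teacher and child characteristics. No term for the teacher is named.

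Under Recruitment overview, "Participants will be recruited via collaborations with preschool groups and independent participants", and the teachers are people the children have not met before. No rule for pairing children with teachers is given.

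**The concern.** If 50 teachers or fewer see 206 children, many children share a teacher. A teacher's own traits are then identical for all of that teacher's children, and the teacher's prompting style is probably similar across them. If the children's outcomes are also correlated within teacher after adjustment, ordinary regression treats repeated information as new information. Its F test rejects too often, and an analysis that allows for the clustering has less power than the calculation promises.

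The sentence on teachers adds to this. It presents a smaller number of teachers as a matter of convenience, whereas the precision of any teacher-driven predictor depends on the number of teachers. That number is settled during recruitment, and no later analysis plan can restore teachers who were not recruited.

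**Working it through.** **Inputs from the article (Sample size section).** R² = 0.09; 12 predictors; 80% power; 5% type I error; 187 children analysed; 206 recruited; at most 50 teachers.

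**Assumed, because the article does not give them.** Residual ICC within teacher of 0.01 to 0.20; 25 teachers as an example of fewer; one teacher per child; equal numbers of children per teacher; how many of the 12 predictors are constant within a teacher.

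**Step 1: reproduce 187.** f² = R²/(1 − R²) = 0.09/0.91 = 0.0989. For the regression F test with u = 12 and noncentrality f²(u + v + 1), 80% power needs v = 173.04, rounded up to 174. N = 174 + 12 + 1 = 187, and the power at 187 is 80.3%. The article's figure is reproduced exactly, with every child counted as an independent observation.

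**Step 2: children per teacher.** 206/50 = 4.12 recruited and 187/50 = 3.74 analysed. With 25 teachers, 187/25 = 7.48.

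**Step 3: type I error of ordinary regression.** Data were simulated with no predictor effect, N = 187 and 12 predictors, at 4,000 runs per cell. The overall F test was applied at the nominal 5% level.

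| Teachers | Predictors at teacher level | ICC 0 | ICC 0.05 | ICC 0.10 | ICC 0.20 |
|---|---|---|---|---|---|
| 50 | 4 of 12 | 4.4% | 6.5% | 8.4% | 13.4% |
| 25 | 4 of 12 | 4.9% | 8.9% | 13.9% | 26.6% |
| 50 | 12 of 12 (worst case) | 4.4% | 9.9% | 17.8% | 34.8% |

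In the rows with 4 of 12, the other eight predictors vary independently of teacher. With no predictor at teacher level and all 12 independent of teacher, the size stays at about 5% at every ICC. Repeat runs differ by about one percentage point; the 13.9% cell, for example, comes out between 14% and 15%.

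**Step 4: power after allowing for clustering.** Design effect = 1 + (m − 1) × ICC, with m = 187/teachers. The effective sample size 187/(design effect) goes back into the F test of step 1. For 50 teachers and ICC 0.05: 1 + 2.74 × 0.05 = 1.137; 187/1.137 = 164.5; power 73.1%.

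| ICC | Power, 50 teachers | Power, 25 teachers |
|---|---|---|
| 0 | 80.3% | 80.3% |
| 0.01 | 78.8% | 76.9% |
| 0.02 | 77.4% | 73.5% |
| 0.05 | 73.1% | 64.1% |
| 0.10 | 66.4% | 51.2% |
| 0.20 | 54.8% | 34.8% |

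These are worst cases. The full design effect applies only when every predictor is constant within a teacher.

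**The case against.** The best counter-argument is that the within-teacher correlation may be very small. Teachers and children have not met before. The executive function tasks are computerised, and a research assistant gives the school readiness screen. The study teacher therefore neither shaped these outcomes beforehand nor scores them, and the usual classroom reason for a sizeable ICC is absent. This stands, and it is why the conclusion is conditional: at ICC 0.01 with 50 teachers, even the worst-case loss is only 80.3 − 78.8 = 1.5 percentage points. It does not show that the ICC is zero. Recruitment through preschool groups could bring children from one preschool to the same teacher, and no pairing rule rules this out.

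Second, many predictors vary by dyad or by child, such as the prompts a child answers or the complexity of the replies. This also stands, so the rows with 4 of 12 predictors at teacher level are a fairer guide than the worst case. The article does not give the actual split.

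Third, model detail may sit in an analysis plan that is not shown. That could cover the choice of model. It does not cover the independence behind 187 or the permission to use fewer teachers, which this article fixes.

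A reader might infer more than the text supports:

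- That the stated power and error rate are simply wrong. This would need an ICC above zero, which the article does not give.
- That the study is underpowered for "How do teacher individual characteristics (e.g., EF, stress, temperament) moderate the relationship between scaffolding and child outcomes". That question is listed as explorative, and power is claimed only for research question 1.
- That the machine-learning models will mix one teacher's children across training and test data. The article describes no such procedure.

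**Conclusion.** The point holds in conditional form. The 80% power and 5% error rate are secured only if the residual within-teacher correlation is about zero, or if the predictors vary independently of teacher. The design makes sharing of teachers unavoidable, and the article neither states nor defends either condition.

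The size of the problem depends on an unknown ICC. It is negligible near zero. At an ICC of 0.05 to 0.20 with 50 teachers, it is a moderate inflation of the test when a third of the predictors sit at teacher level, and a marked loss of power in the worst case. At any ICC above zero, both grow as the number of teachers falls, which is the direction the recruitment sentence allows.

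**What to change.** - **Analysis.** For research question 1, replace standard regression with a mixed model that has a teacher random intercept and small-sample degrees of freedom, or keep the regression and use cluster-robust errors.
- **Power.** Restate the power of the planned 187 children over a stated ICC range and the expected number of teachers. Say that precision for teacher-level predictors depends on the number of teachers.
- **Teachers.** Remove the suggestion that fewer teachers can be used without loss.

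These are changes of wording in two sections and need no extra children. The cost is a less favourable power statement. Holding 80% in the worst case with 50 teachers would take 219, 269 or 594 analysed children at ICC 0.05, 0.10 or 0.20; this is not proposed. A preschool random intercept is optional. A fixed limit on children per teacher is also optional and would need care, since 50 × 4 = 200 falls short of 206.

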### Teacher-child interaction tasks

#### Cooperation task.

This task was adapted from Reindl and colleagues [54]. A teacher and child will manipulate their respective on-screen animal using a keypress to catch a ball together. They will be instructed to press their keys in-time to “catch the ball together”. If the difference between the teacher and child’s key presses falls below a cut-off, the dolphins will jump together. If the difference is above the cut off, the faster respondent’s dolphin will catch the ball alone. The threshold was set to T =  1+ 1/8 (RT1 + RT2), where RT1 and RT2 are the response times of the two participants. This task will be split into 2 phases: teaching phase and test phase. During the teaching phase, the teacher and child can talk to discuss the best strategy to achieve the highest possible score, whereas the teacher and child are asked to complete the test phase in complete silence. Both phases will consist of 20 trials. In the test phase, a point will be awarded when the pair catch the ball together and a point will be deducted on trials when only one player catches the ball. The pair will start with a score of 100. Participants will be seated side-by-side facing a computer monitor with a divider between them. The divider will prevent the teacher and child looking at each other’s hands and will allow them to see the other player’s face.

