#### Storybook reading task.

In this storybook reading task, the teacher and child will read a digital storybook for approximately 4 min and 30 seconds, adapted from [55]. The story, *Sally’s Space Adventure*, was designed to expose children to novel object label mappings, with objects and labels were chosen from the Novel Object and Unusual Name (NOUN) database [56]. *Sally’s Space Adventure* follows a narrative of an astronaut travelling through space to find the four novel objects needed to fix a broken rocket. All novel objects are named three times during the story: once with a colourful backdrop, once in isolation with a black backdrop, and once later in the story with an assigned function (e.g., fixing the engine of the rocket). The order and combination of novel words and novel objects will be fully randomised across participants. Teachers will not be instructed on how to engage with the child to preserve the natural dynamics of their student-teacher interactions while reading.

Children’s learning and retention of story information during the shared book reading will be assessed using a narrative recall exercise and a short quiz delivered by the teacher immediately after the story reading has finished.

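### At least 156 of 206 dyads will have a teacher who has already done the tasks, so dyad order within teacher may affect both sides of the RQ2 analyses and should be logged and modelled

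*Protocol article*

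**What the plan says.** Under Sample size, the article sets the child target: "To account for attrition an additional 10% will be recruited to give a final sample size of 206 children". On teachers it says "Up to 50 preschool teachers will be recruited", and that "fewer teachers may be required if they elect to take part with several children". No maximum number of children per teacher is given. Under Recruitment overview: "Participants will be preschool children aged 2–7 years and previously unacquainted preschool teachers". That controls a teacher's familiarity with the child, not with the tasks.

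The task sections describe a single set of materials:

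- **Storybook reading task.** One named story, which "follows a narrative of an astronaut travelling through space to find the four novel objects needed to fix a broken rocket". Within it, "The order and combination of novel words and novel objects will be fully randomised across participants". The teacher reads in an uninstructed style and then gives the recall exercise and quiz.
- **Cooperation task.** One game with a joint score. The cut-off for a joint catch is computed from both players' response times. In the teaching phase "the teacher and child can talk to discuss the best strategy to achieve the highest possible score".
- **Creative problem solving tasks.** Four Tangram sets, one per phase. The teacher demonstrates in practice and gives verbal feedback in the second test phase. No rotation of sets across children is described.

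The Analysis plan uses teacher prompts and signals as predictors of child executive function (EF) and school readiness for RQ1. For RQ2 it relates neural coupling to learning on the scaffolding tasks and to the behavioural indices. The exploratory questions relate scaffolding form to behavioural or neural synchrony.

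**The concern.** Repeat participation is worded as something teachers may elect, but the article's own numbers make it the usual case. From the second child on, the teacher knows the narrative, the quiz format, the puzzle solutions and the game.

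The teacher is also part of what is measured. Teacher timing enters the joint cooperation score, teacher prompts are the scaffolding indices, the teacher delivers the quiz, and half of each dyadic EEG recording is the teacher's. Experience can therefore reach both variables in an RQ2 or scaffolding-synchrony association. If both drift with the teacher's repetition number, part of the observed association reflects rehearsal rather than interaction quality.

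This is distinct from clustering. A teacher-level term allows for stable differences between teachers but leaves a trend within a teacher untouched.

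**Working it through.** **The plan's own figure.** Inputs from Sample size: R² = 0.09, 12 predictors, 80% power, 5% type 1 error. Then f² = 0.09/0.91 = 0.0989. With N = 187 the denominator degrees of freedom are 187 − 12 − 1 = 174, the noncentrality is 0.0989 × 187 = 18.5, and the power of the overall F test is 0.803. So 187 reproduces. Adding 10% gives 187 × 1.10 = 205.7, rounded up to 206. The present point does not alter these figures.

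**How many dyads have an experienced teacher.** With one teacher per child, each teacher contributes at most one first dyad.

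- 50 teachers, 206 children: 206 − 50 = 156, and 156/206 = 75.7%. Average children per teacher: 206/50 = 4.12.
- 50 teachers, 187 evaluable children: 187 − 50 = 137, and 137/187 = 73.3%. Average: 187/50 = 3.74.
- Fewer teachers (assumed numbers), 206 children: 5.2 per teacher at 40, 6.9 at 30, 10.3 at 20.

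Four per teacher is thus roughly the lowest average the plan allows. The spread across teachers is not fixed.

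**What drift would do to an association.** The documents give no practice effect, so this is an illustration. Let an index and a score each equal b × (order position) plus independent noise with SD 1. For m children per teacher, Var(position) = (m² − 1)/12, which is 1.25 for m = 4 and 6.67 for m = 9. With no true association,

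r = b² Var / (1 + b² Var).

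| Drift b (SD per child) | m = 4: first-to-last shift | m = 4: induced r | m = 9: first-to-last shift | m = 9: induced r |
|---|---|---|---|---|
| 0.1 | 0.3 SD | 0.0125/1.0125 = 0.012 | 0.8 SD | 0.0667/1.0667 = 0.063 |
| 0.2 | 0.6 SD | 0.05/1.05 = 0.048 | 1.6 SD | 0.2667/1.2667 = 0.211 |
| 0.3 | 0.9 SD | 0.1125/1.1125 = 0.101 | not shown | not shown |

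Nine children each corresponds to about 23 teachers (206/9 = 22.9). If the two variables drift in opposite directions, the induced r has the same size and a negative sign.

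**Where the mechanism applies.**

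- **RQ1.** Child EF is measured on a touch-screen computer, and school readiness is tested by a research assistant. Neither has a described route from teacher repetition. If only the predictor drifts, the induced r is zero and a true correlation is multiplied by 1/√(1 + b² Var). At b = 0.2 and m = 4 that is 1/√1.05 = 0.976, a small loss. Bias needs a further link, such as order position tracking child age within the 2 to 7 year range.
- **RQ2, task scores, and scaffolding against synchrony.** Both variables involve the teacher's behaviour or brain signal during the repeated tasks, so both can drift.
- **RQ2, EF and school readiness.** The stated research question also names these as outcomes. For them the RQ1 reasoning applies, so RQ2 is exposed only in part.

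**The case against.** The strongest reply is that the effect is probably small and the design already limits it. Much of this stands.

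- **Size.** At four children per teacher, drifts of 0.1 to 0.2 SD per child induce correlations of only 0.01 to 0.05. Larger values need a long, steady drift with no plateau, in both variables.
- **Direction.** Practice might raise scores. Re-randomised word-object pairings might instead cause interference between children and lower them. The documents support a possible shift, not a demonstrated one.
- **Existing protection.** Randomising the pairings limits carry-over of specific answers. The first Tangram test phase has no teacher feedback, and the third has minimal guidance. None of this removes familiarity with the narrative, quiz format, puzzles or game.
- **Unseen documents.** An order term may be in a full analysis plan, and teacher orientation may be in a full protocol. Their absence from an article is not itself an error. What the article does fix is the teacher-to-child ratio, open-ended reuse and, as described, one set of materials. How child ages fall across order positions is settled at scheduling and cannot be restored by analysis.
- **Accepted trade-off.** The limitations section gives up experimental control for natural interaction. It speaks of differences between dyads, not of teacher repetition.

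A reader might also set the induced association beside the 9% of variance used for sizing. That comparison does not hold. The 9% belongs to RQ1, whose outcomes practice has no described route to, whereas the induced correlation concerns RQ2 task scores and synchrony. Nor do the documents show that teachers who see more children differ in their characteristics.

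**Conclusion.** The point holds as an uncontrolled risk to the RQ2 task-score analyses and the exploratory scaffolding-synchrony analyses. That most dyads have an experienced teacher follows from the plan's own numbers: at least 156 of 206, assuming full recruitment and one teacher per child. The size and sign of any resulting bias are unknown. Under the assumed equal linear drift it is small at about four children per teacher (r about 0.01 to 0.10 for 0.1 to 0.3 SD per child). It becomes material if fewer teachers each see many more children (about 0.06 to 0.21 for 0.1 to 0.2 SD over nine).

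A reader might infer that practice does shift the indices and scores, or that the RQ1 findings would be spurious. The documents support neither. For RQ1 the expected effect is mainly noise in the predictors, unless dyad order is related to child age. The sample-size figure is unaffected.

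**What to change.** 1. Log each dyad's order number within teacher, including for dyads already collected where dates allow.
2. Include order number as a covariate in the RQ2 and scaffolding-synchrony models, alongside whatever term handles teacher clustering. Add it to the RQ1 models as a sensitivity term.
3. When scheduling, spread child ages across order positions within teacher so that order does not stand in for age.

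The cost is one logged variable, one degree of freedom per model and a minor scheduling constraint. A linear term would capture a plateauing effect only in part.

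Two other remedies are not recommended as requirements. An analysis of first dyads only would have at most 50 children, against the 187 the regression was sized on, and is too small to be informative. A compulsory familiarisation run trades away the teacher's unrehearsed encounter and would not stop drift across later children.
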